### Safety assessment

2.7

We will closely monitor the safety of heat-sensitive moxibustion throughout the study. Any adverse events (AEs) that are not related to the natural progression of hypertension will be recorded and reported to the Ethics Committee regularly. If a serious AE that leads to hospital admission, disability, a threat to life, or death occurs, we will report it to both the Ethics Committee and the Food and Drug Administration of Jiangxi Province within 24 hours.

We will also assess to what degree each AE is related to heat-sensitive moxibustion according to the following considerations^[19]^:

(1)whether there are time and position correlations between the AE and heat-sensitive moxibustion;(2)whether the AE cannot be explained by other factors;(3)whether the AE is alleviated or disappears when heat-sensitive moxibustion is stopped;(4)whether the AE reappears when heat-sensitive moxibustion is administered again; and(5)whether the AE can be explained by biological or pharmacological mechanisms.

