#### Primary outcomes

2.6.1

(1)Changes in SBP and DBP (mm Hg) measured with an electronic sphygmomanometer. The average value of 3 measurements will be used.(2)Percentage changes in the dose of antihypertensive drugs. At each regular visit, the community doctors will determine whether the dose of antihypertensive drugs needs to be adjusted according to changes in blood pressure during the last month and will record the adjustment.

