### Study visits

2.8

During the 1-year follow-up period, the investigators will visit the patients monthly at the community health service centers, which are generally within 1 km of the patients’ homes. At month 0 (baseline visit), we will collect demographic characteristics (name, phone number, sex, age, education level, height, and weight) and disease-related characteristics (SBP, DBP, course of hypertension, comorbidities, smoking, drinking, and type and dosage of antihypertensive drugs currently used). At months 6 and 12, we will measure blood pressure, changes in doses of antihypertensive drugs, quality of life, blood and urine indicators, and AEs. The other regular visits (ie, months 1–5 and 7–11) will involve the distribution of moxa rolls and moxibustion boxes to patients, the assessment of patient compliance and the adjustment of the doses of antihypertensive drugs. A detailed schedule of the study visits is shown in Figure 2.

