## Discussion

3

Although acupuncture has long been used to treat hypertension, and there is no lack of evidence supporting its efficacy, it is invasive and must be performed by qualified doctors.^[20]^ Therefore, acupuncture cannot be self-administered by patients or used as a long-term therapy. Heat-sensitive sensitive moxibustion is a noninvasive therapy, and patients can easily learn how to administer it and reach an expected level of efficacy after training. Self-administered moxibustion is also quite inexpensive, costing only approximately 30 Chinese yuan (4 dollars) per month. If our study verifies that heat-sensitive moxibustion does have a significant efficacy for the treatment of hypertension, it may be able to partially replace antihypertensive drugs, reduce medical costs, and serve as a long-term therapy in the community setting. Although a randomized controlled trial is the gold standard for establishing the efficacy of any therapy, it may be ethically problematic without preexisting efficacy and safety evidence. Therefore, this nonrandomized pragmatic study also aims to provide an ethical basis for further randomized controlled trials.

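### Section 2.7 screens adverse events by presumed cause before they are recorded, so clinical events from poorer blood-pressure control can drop out of the safety record

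*Protocol article*

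**What the plan says.** The Safety assessment section (2.7) sets the recording rule: "Any adverse events (AEs) that are not related to the natural progression of hypertension will be recorded". Periodic reports of these events go to the ethics committee. The next sentence deals with serious events and sets a 24-hour limit for notifying the ethics committee and the provincial regulator: "If a serious AE that leads to hospital admission, disability, a threat to life, or death occurs, we will report it". The section then turns to causality: "We will also assess to what degree each AE is related to heat-sensitive moxibustion", using five considerations.

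Three other places bear on this rule:

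- Primary outcomes (2.6.1) include blood-pressure change and percentage change in antihypertensive dose. For the regular visits, the section states: "the community doctors will determine whether the dose of antihypertensive drugs needs to be adjusted according to changes in blood pressure during the last month".
- Study visits (2.8) lists the measurements at months 6 and 12 as blood pressure, dose changes, "quality of life, blood and urine indicators, and AEs". For months 1–5 and 7–11 the text names distribution of materials, compliance and dose adjustment.
- The Discussion says that, if efficacy is verified, "it may be able to partially replace antihypertensive drugs".

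**The concern.** The exclusion acts when an event is recorded. It is not a causality label attached to an event already in the database. An event judged to be progression of hypertension therefore leaves no trace under this rule, and no later analysis can bring it back.

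The events most easily judged that way are also the ones a reader would want compared in this trial. Doses can move during follow-up, dose change is a primary outcome, and less drug use is a hoped-for later benefit. If control worsened in some patients, it would show clinically as symptoms or complications of hypertension. The Introduction itself names cardiovascular events and early death as consequences of the disease.

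Safety is a stated objective. The data monitoring committee may stop the study on safety results (2.10), and the closing paragraph of the Discussion expects the findings to reach public health decisions. All of these uses would rest on a record already screened by cause.

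**Working it through.** The plan states no figure for this point, so there is none to reproduce. The check sets the sections side by side.

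1. **Is the excluded class defined?** No. Section 2.7 does not say what natural progression covers, who decides it, or how it differs from deterioration after a dose change. In a single patient the two will often look the same.

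2. **Who is in a position to decide, and do they know the group?** Patients choose their group (2.4). Community doctors train the moxibustion patients one-on-one (2.4), decide on dose adjustments (2.6.1) and collect the data (2.10). Investigators see the patients at monthly visits and check the used moxibustion boxes (2.8, 2.9). Whichever of them decides, the group is known. Section 2.10 conceals the grouping from the analysts, but that comes after recording.

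3. **Are the excluded events caught elsewhere?** Partly. "Changes in SBP and DBP (mm Hg) measured with an electronic sphygmomanometer" and drug dose are primary outcomes. Urinary albumin, serum creatinine and a hypertension-specific quality-of-life scale are secondary outcomes (2.6.2). Stroke, infarction, hypertensive crisis and hospital admission appear in neither outcome list.

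4. **Does the serious-event sentence close the gap?** It defines seriousness by consequence and does not repeat the exclusion, but it does not say that the exclusion is lifted. Both readings are possible. Non-serious events are excluded on either reading.

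5. **What happens to a between-group comparison?** Let p_M and p_C be the shares of hypertension-related events classed as progression in the moxibustion and control groups. Then

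   recorded risk ratio = true risk ratio × (1 − p_M) / (1 − p_C).

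   If the shares are equal, the ratio is preserved and only events are lost. If they differ, which is possible when whoever classifies the event knows the group, the ratio is biased. The protocol fixes neither share.

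6. **How many events could be at stake?** The documents give no rate, so the following rates are assumptions. With 300 patients per group (2.11), events per group = 300 × rate:
   - 0.5%: 300 × 0.005 = 1.5
   - 1%: 300 × 0.01 = 3
   - 2%: 300 × 0.02 = 6
   - 3%: 300 × 0.03 = 9

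   These are the events that would depend on this classification. They are not a forecast of events lost. With counts this small, a few classifications could change the picture.

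7. **Timing.** In the text of 2.8, adverse events are listed at 2 of the 12 monthly follow-up visits, leaving 5 + 5 = 10 without them. Section 2.7 promises monitoring throughout the study. The detailed schedule is in Figure 2, which is not available here, so the count describes the text only.

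**The case against.** The strongest counter-argument is that the rule is narrower than it looks. Read literally, harm from a reduced dose is not natural progression and would be recorded. Strokes, infarctions and crises would usually meet the definition of a serious event, which carries no exclusion by cause and requires reporting within 24 hours. Worse control would show in blood pressure, dose and renal markers. Patients with earlier serious cardiovascular or cerebrovascular events are excluded (2.3), and follow-up lasts one year.

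Much of this stands, and it rules out several stronger readings that a reader might infer:

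- *That strokes or crises will never enter the data.* The text does not support this. For serious events there is an ambiguity, not a demonstrated loss.
- *That declining renal function or rising blood pressure goes unseen.* Both are measured as outcomes in both groups.
- *That one arm is designed to receive less drug treatment.* Section 2.5 has both groups maintain their original drugs, and dose adjustment in 2.6.1 is not restricted to one group. The remark in the Discussion about replacing drugs is conditional and looks beyond the trial.
- *That adverse events go unasked at ten visits and minor burns will be missed.* Figure 2 may list them. The text of 2.8 also appears incomplete, since it lists follow-up blood pressure only at months 6 and 12 while 2.6.1 adjusts doses on the last month's changes. Section 2.9 provides consultations and physical examinations at every visit.
- *That causality assessment ignores drug changes.* The second consideration in 2.7 asks about other explanations, which leaves room for a dose change. A separate assessment against dose change would be useful but is optional.

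The objection does not remove the core point. The literal reading requires a distinction that the protocol does not define and that can rarely be drawn in one patient. Expedited reporting to authorities is also not the same as a recorded safety comparison between groups.

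**Conclusion.** The concern holds in a limited form. Section 2.7 applies an undefined, cause-based filter when events are recorded, and those placed to apply it know the group. Symptoms and clinical events from poorer blood-pressure control can be left out of the safety record. This is clear for non-serious events and uncertain for serious ones. The possible bias in the group comparison has no fixed direction or size, because the documents give neither event rates nor the share that would be classed as progression. The range of 1.5 to 9 events per group rests wholly on the assumed rates of 0.5% to 3%.

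The conclusion rests on two assumptions: that the rule is followed as written, and that the staff who see the patients decide which events count as progression. The second is an inference from 2.4, 2.6.1, 2.8 and 2.10, since no section names who decides. The timing issue is secondary. It is an apparent mismatch between 2.7 and the text of 2.8 that Figure 2 may already resolve.

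**What to change.** - Delete the exclusion in 2.7. Record every adverse event and serious adverse event in both groups, whatever the presumed cause.
- State explicitly that no cause-based exclusion applies to serious adverse events.
- Classify the relation to hypertension, drug change or moxibustion after recording, as a separate field.
- Compare cardiovascular, cerebrovascular and hypertensive events between the groups as originally chosen.
- Reconcile 2.8 with 2.7 by adding an adverse-event question to each existing monthly visit, and align Figure 2 if it differs.

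The cost is a reworded section, one item on the monthly form, and more events to log and report. No new visits are needed and no treatment changes. The change should be made before data collection, because events left unrecorded cannot be reliably recovered later.

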### Study visits

2.8

During the 1-year follow-up period, the investigators will visit the patients monthly at the community health service centers, which are generally within 1 km of the patients’ homes. At month 0 (baseline visit), we will collect demographic characteristics (name, phone number, sex, age, education level, height, and weight) and disease-related characteristics (SBP, DBP, course of hypertension, comorbidities, smoking, drinking, and type and dosage of antihypertensive drugs currently used). At months 6 and 12, we will measure blood pressure, changes in doses of antihypertensive drugs, quality of life, blood and urine indicators, and AEs. The other regular visits (ie, months 1–5 and 7–11) will involve the distribution of moxa rolls and moxibustion boxes to patients, the assessment of patient compliance and the adjustment of the doses of antihypertensive drugs. A detailed schedule of the study visits is shown in Figure 2.

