### Training and assignment

2.4

There is a community health service center in each community. Before the study begins, we will invite senior experts to give 4 lectures (once per week) for residents in each community health service center to introduce the principal and anticipated efficacy of the use of heat-sensitive moxibustion for the management of hypertension. After fully comprehending the relevant knowledge, eligible patients will enter the heat-sensitive moxibustion group or the control group according to their preferences. Investigators and community doctors will not provide any advice regarding the group selection. For patients entering the heat-sensitive moxibustion group, community doctors will further provide one-on-one training, explaining how to perform heat-sensitive moxibustion, how to identify heat-sensitive acupoints, and how to avoid burns, among other safety precautions.

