### Interventions and co-interventions

2.5

Patients in the heat-sensitive moxibustion group will self-administer heat-sensitive moxibustion for one year while maintaining their original antihypertensive drugs. With the doctors’ help, the patients will first identify the heat-sensitive acupuncture points near CV8 (Shenque, the center of the navel), CV4 (Guanyuan, approximately 10 cm below the navel), and bilateral ST36 (Zusanli, approximately 7 cm below the lateral of the knee) and then perform moxibustion on the heat-sensitive acupoints. Self-sticking mini-moxa rolls will be used as the combustible material, which can be placed and burned in a moxibustion box (Fig. 2). A matching velvet bag can be used to wrap the moxibustion box to avoid burns. The suggested dose of moxibustion will be one moxa roll (approximately 30 minutes) per session, with 1 session per day and 7 sessions per week. Driven by a pragmatic design, we will allow the patients to adjust the dose of moxibustion to make it convenient, but they need to truthfully report the adjusted dose. Patients in the control group will only maintain their original antihypertensive drugs and will not perform heat-sensitive moxibustion. There will be no restriction on the type and dose of antihypertensive drugs, but other acupoint stimulation therapies, such as acupuncture, will be prohibited.

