In 2017, the government of Xiashan District in Weifang city in Shandong Province tried for the first time to popularize heat-sensitive moxibustion as a daily health care method for all residents of the town. The measures taken to popularize the knowledge of heat-sensitive moxibustion included building a community center dedicated to providing free sessions of heat-sensitive moxibustion, organizing expert lectures, training patients on-site, and providing free moxibustion materials. After 2 years of efforts, the popularization work achieved satisfactory results – heat-sensitive moxibustion was practiced by 67% of the total population of 62,000 people. In addition, the per capita medical expenditure decreased by 49.8% and the number of annual outpatient consultations decreased by more than 16.7% compared with the values 2 years before.^[21]^ Unfortunately, no rigorous evidence was obtained regarding the effects of heat-sensitive moxibustion on hypertension with the exception of scattered case reports published during the popularization campaign. Learning from the successful experience in Shandong Province, the government of Jiangxi Province started to promote a public health project called “Everyone Uses Heat-sensitive Moxibustion, Everyone Enjoys Health” in several cities in 2019. Currently, the project is progressing smoothly. It could provide a favorable climate for the recruitment of participants and the successful completion of this study.

This study has potential limitations. The reduction of internal validity caused by the nonrandomized design is the main limitation. Although we have expanded the expected sample size as much as possible and will adjust for multiple confounders in the statistical analysis, the bias caused by unknown confounders cannot be completely avoided. However, the extrapolation of the results of this study, as a major advantage of a pragmatic study, will be enhanced. Another limitation is that it may be difficult for patients to remain compliant with the heat-sensitive moxibustion protocol for 1 year, and poor compliance will introduce bias. However, an important purpose of this study is to evaluate the feasibility of heat-sensitive moxibustion self-administration as a long-term intervention in patients in the community with hypertension. If compliance is poor, it will show that this is not a feasible strategy.

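### Patients choose their own group, but the listed data and the adjustment set include no physical activity or salt/diet item, and weight is listed only at month 0 and is not in the models

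*Protocol article*

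**What the plan says.** Section 2.4 (Training and assignment) states that "eligible patients will enter the heat-sensitive moxibustion group or the control group according to their preferences". The choice follows four lectures given "to introduce the principal and anticipated efficacy of the use of heat-sensitive moxibustion for the management of hypertension". Section 2.5 suggests "one moxa roll (approximately 30 minutes) per session, with 1 session per day and 7 sessions per week" for the moxibustion group over one year, and lets patients adapt this for convenience.

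Section 2.8 (Study visits) lists what is recorded:

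- **Month 0:** basic demographics, with body weight and height among them. The clinical items of that visit are given as "disease-related characteristics (SBP, DBP, course of hypertension, comorbidities, smoking, drinking, and type and dosage of antihypertensive drugs currently used").
- **Months 6 and 12:** "At months 6 and 12, we will measure blood pressure, changes in doses of antihypertensive drugs, quality of life, blood and urine indicators, and AEs".
- **Other monthly visits:** handing out materials, plus "the assessment of patient compliance and the adjustment of the doses of antihypertensive drugs".

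Section 2.12 adjusts the ANCOVA and logistic models for eight items: age, duration of hypertension, starting SBP, comorbid conditions, education, smoking, drinking and antihypertensive drug types. Weight and height are collected but are not among them. Section 2.11 explains that the sample was raised from 140 to 300 per group so that more confounders could be adjusted for. The Discussion concedes that "the bias caused by unknown confounders cannot be completely avoided".

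**The concern.** The groups are separated by the patient's own readiness to take on a regular home routine. That this readiness goes with readiness to exercise more or eat less salt is an inference, but a reasonable one. Physical activity and salt intake are known influences on blood pressure and can be asked about, so they are not the unknown confounders that the Discussion concedes.

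Two things are at stake. First, baseline differences in activity, diet and body weight are controlled only as far as baseline SBP and the other listed covariates happen to carry them. Second, if lifestyle changes differently in the two groups during the year, SBP, DBP, drug dose, glucose and lipids could all move in the same direction. Agreement across these outcomes might then be read as confirmation of a moxibustion effect, and the listed data contain no direct measure of lifestyle change to set against that reading.

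**Working it through.** **Step 1: compare the lists.** Sources are sections 2.8 and 2.12.

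| Item | Month 0 | Months 6 and 12 | In the models |
|---|---|---|---|
| Smoking, drinking | listed | not listed | yes |
| Weight, height | listed | not listed | no |
| Physical activity | not listed | not listed | no |
| Salt or diet | not listed | not listed | no |

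The models can use only what is collected. Baseline weight or BMI could enter them today; activity and salt/diet could not, on the listed data.

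**Step 2: inputs for an illustration.** From section 2.11: SD 20 mm Hg, target difference 5 mm Hg, 300 per group, 20% attrition, hence 300 × 0.80 = 240 completers per group. Assumed, not in the documents: a lifestyle change lowers SBP by L = 3 to 5 mm Hg, and its uptake is d = 0.20 to 0.40 higher with moxibustion.

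The plan's own calculated figure, 140 per group, is not an input. The usual two-sided two-sample formula with these values gives 252 per group, and 252 / 0.80 = 315 after attrition, so 140 is not reproduced. That is a separate matter and does not bear on this point.

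**Step 3: bias.** Bias = L × d.

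- Low end: 3 × 0.20 = 0.6 mm Hg, which is 0.6 / 5 = 12% of the target.
- High end: 5 × 0.40 = 2.0 mm Hg, which is 2.0 / 5 = 40% of the target.
- A wider range, L = 2 to 6 and d = 0.10 to 0.50, gives 0.2 to 3.0 mm Hg, or 4% to 60% of the target.

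**Step 4: chance of p < 0.05 with no moxibustion effect.** SE = 20 × √(2/n), which is 1.826 at n = 240 and 1.633 at n = 300. The rejection rate is Φ(bias/SE − 1.96) + Φ(−bias/SE − 1.96).

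| Bias (mm Hg) | 240 per group | 300 per group |
|---|---|---|
| 0 | 5.0% | 5.0% |
| 0.6 | 6.2% | – |
| 1.0 | 8.5% | 9.4% |
| 2.0 | 19.5% | 23.2% |
| 3.0 | 37.6% | 45.1% |

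For a given bias the larger sample raises the false-positive rate. Extra patients help against confounding only if the confounders are measured and put in the model.

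**Step 5: opposite direction.** If patients who add moxibustion make fewer lifestyle changes, the same sizes work against it: a true 5 mm Hg difference would appear as 5 − 0.6 = 4.4 down to 5 − 2.0 = 3.0 mm Hg.

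**The case against.** - **The article is condensed.** The visit schedule in Figure 2 and the case report forms are not shown, and section 2.9 offers physical examinations at the visits, where weight may well be taken. A reader might infer that activity, diet and follow-up weight are never collected. The text supports only that they are not listed. The objection stands on that wording, but it does not answer the adjustment set in section 2.12, which is stated item by item and omits weight although weight is collected.
- **Confounding is already admitted.** The Discussion calls the nonrandomized design the main limitation, section 3 presents the study as groundwork for randomized trials, and the models already hold eight items, including smoking and drinking. This is fair as context. The residual bias conceded is that from unknown confounders, however, and these are known ones.
- **The size is assumed.** This stands in full. Only the SD, target, sample size and attrition come from the protocol. At the low end the false-positive rate barely exceeds 5%.
- **Baseline covariates cannot correct later change.** This also stands. Restricting to patients whose lifestyle did not change would be no cure: it conditions on behaviour after group choice, can introduce selection bias, and may remove part of the pragmatic effect if the programme itself alters habits.
- **Other data give some signal.** Glucose, HbA1c and lipids at months 6 and 12 may partly reflect lifestyle change. But they are secondary outcomes, so they cannot serve as independent evidence about it.

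**Conclusion.** The point holds in limited form. With groups formed by preference, the listed data and the stated models leave physical activity, salt/diet and body weight uncontrolled, and they give no direct way to describe differing lifestyle change. The missing weight term is the firmest part, because it needs no assumption about forms that are not shown.

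The 0.6 to 2.0 mm Hg bias, and the false-positive rate of about 6% to 19.5% at 240 per group, illustrate what could happen. They rest on assumed lifestyle effects and uptake gaps, on an assumed direction, and on the protocol's SD of 20 mm Hg. A reader might infer that any benefit found would be a lifestyle artefact. The documents do not support that: they contain nothing on lifestyle differences between the groups, and the bias could equally hide a benefit. This is a worthwhile, inexpensive improvement to an openly nonrandomized study. It does not invalidate the design.

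**What to change.** 1. Add one physical-activity item and one salt/diet item to the month-0 form, completed before the patient chooses a group. If the full forms already hold them, say so and go to step 2.
2. Include both items, together with the baseline weight or BMI already collected, in the ANCOVA and logistic models of section 2.12.
3. Repeat activity, salt/diet and weight at months 6 and 12, and report their change by group descriptively only. Do not adjust for these values or restrict on them in the main analysis, since they arise after group choice.
4. In the Discussion, name lifestyle as a known source of residual confounding.

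Cost: a few questions and a weight reading at visits that already take place, and a few model degrees of freedom out of about 2 × 240 = 480 completers. Self-report is imperfect and some confounding will remain, particularly from lifestyle change after baseline. The baseline items need to be in place before enrolment, because they cannot be reliably recovered afterwards.

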#### Secondary outcomes

2.6.2

(1)Quality of life will be assessed by a validated patient-reported outcome scale,^[18]^ which includes 27 items and assesses the impacts of hypertension on the 3 dimensions of quality of life, namely, the physical dimension (18 items), psychological dimension (4 items), and family-social dimension (5 items). Each item is divided into 5 categories, with each category receiving 0 to 4 points in sequence. A higher score indicates a worse quality of life. The total score equals the sum of the score of each item, ranging from 0 to 108 points. The detailed content of the scale is provided in the Supplemental Content (http://links.lww.com/MD/E870). We will also analyze the scores of individual dimensions separately.(2)Indicators related to diabetes mellitus, including changes in fasting blood glucose (mg/dl) and hemoglobin A1c (%), will be assessed.(3)Indicators related to dyslipidemia, including changes in total cholesterol (mg/dl), triglycerides (mg/dl), low-density lipoprotein cholesterol (mg/dl), and high-density lipoprotein cholesterol (mg/dl) levels, will be assessed.(4)Indicators related to hypertensive renal disease, including urinary albumin (g/l) and serum creatinine (μmol/l) levels, will be assessed.(5)Patient compliance will be determined. Patient compliance will be deemed poor if a patient administers heat-sensitive moxibustion fewer than 8 times per month. The proportion of patients with poor compliance will be assessed.

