### Compliance enhancement

2.9

By default, we will provide patients in the heat-sensitive moxibustion group with 120 moxa rolls and 4 moxibustion boxes for free each month. If the moxibustion materials are insufficient because some are lost or for other reasons, patients can apply to receive more materials for free. When the patients return for a visit, they need to return the moxibustion box used last month to receive new moxibustion boxes. The investigators will determine whether the dose of moxibustion reported by the patients is consistent with the degree of blackening of the moxibustion boxes by the soot produced by burning the moxa. Patients in both groups will receive free health consultations and physical examinations at each visit and a reward of 100 and 200 Chinese yuan when the 6- and 12-month visits are completed, respectively. Of course, patients can voluntarily withdraw whenever for whatever reason during the study, and withdrawal will not affect any subsequent treatment.

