### Statistical analysis plan

2.12

The analyses of the primary outcomes will be performed in the intention-to-treat population where either patients in the control group who performed heat-sensitive moxibustion or patients in the heat-sensitive moxibustion group who stopped moxibustion during follow-up will still be kept in their original group. Meanwhile, we will also perform sensitivity analyses using the perprotocol population to test the robustness of the main analysis. All analyses of the secondary outcomes will be performed in the per-protocol population. We will decide whether to impute missing data and which method should be used to impute missing data based on the actual distribution of the missing data.

For categorical or ordinal variables, we will calculate frequencies and percentages as the descriptive statistics and compare the between-group differences using the chi-square test or the linear-by-linear association test. We will present the means with standard deviations/errors and medians with interquartile ranges for continuous variables with normal and skewed distributions, respectively; the independent *t* test or the Mann-Whitney *U* test will be used to compare 2 groups. The effects of heat-sensitive moxibustion on the outcomes will be inferred using analysis of covariance or a logistic regression model adjusted for age, course of hypertension, baseline SBP, comorbidities, education level, smoking status, drinking status, and types of antihypertensive drugs recoded as dummies. The effects will be measured as the mean difference or odds ratio with a 95% confidence interval, and *P*-values will also be calculated. In addition, we will test 2 subgroup hypotheses:

(1)the dose of moxibustion: ≥3 sessions/wk vs <3 sessions/wk;(2)whether the heat-sensitive sensation appears: yes vs no.

The significance level indicating a difference between groups and subgroups will be α = 0.05. We will use R version 4.0.2 (The R Foundation for Statistical Computing, Austria) to run all statistical analyses.

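### Glucose and lipid comparisons between self-selected groups are open to confounding by glucose- and lipid-lowering drugs, which are not among the listed data items or in the stated covariate set

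*Protocol article*

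**What the plan says.** All references are to the protocol article.

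- **Outcomes (2.6.2).** The second group of secondary outcomes reads "Indicators related to diabetes mellitus, including changes in fasting blood glucose (mg/dl) and hemoglobin A1c (%), will be assessed". The third covers change in total, LDL and HDL cholesterol and in triglycerides.
- **Allocation (2.4).** After the lectures, "eligible patients will enter the heat-sensitive moxibustion group or the control group according to their preferences".
- **Data items (2.8).** The baseline list includes comorbidities, and its only drug item is "type and dosage of antihypertensive drugs currently used". At months 6 and 12, and at the visits in between, the drug items are changes or adjustments in antihypertensive dose.
- **Co-interventions (2.5).** The text covers antihypertensives, which are unrestricted, and other acupoint therapies, which are barred. It does not mention glucose- or lipid-lowering drugs.
- **Eligibility (2.3).** Neither diabetes nor dyslipidaemia is named as an exclusion.
- **Model (2.12).** One covariate set serves all outcomes. It holds age, hypertension duration, baseline SBP, comorbidities and education, and ends with "smoking status, drinking status, and types of antihypertensive drugs recoded as dummies". No other drug class appears.

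**The concern.** Glucose-lowering and lipid-lowering drugs act directly on the outcomes in question. Patients may be taking them at entry, or may begin or change them during the year. Because patients choose their group, nothing in the design balances this use. The study's protection is covariate adjustment, and section 2.11 justifies the larger sample on that ground. Yet the stated model leaves out an obvious determinant of HbA1c and LDL cholesterol that could be measured.

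The comorbidity covariate helps in part. It can show that a patient has diabetes, but not whether the diabetes is treated or whether treatment changed between baseline and month 12. For an outcome defined as a change, a new or altered drug matters most. At stake is a difference in HbA1c or LDL cholesterol being credited to moxibustion, or a real one being hidden, because drug treatment differed between the groups. A larger sample does not shrink such a bias.

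**Working it through.** **Comparison of the lists**

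| Element | Antihypertensives | Glucose-lowering drugs | Lipid-lowering drugs |
|---|---|---|---|
| Matching outcome (2.6) | SBP, DBP, dose | Glucose, HbA1c | Four lipids |
| Listed at baseline (2.8) | Yes | No | No |
| Listed in follow-up (2.8) | Yes | No | No |
| In the covariate set (2.12) | Yes (types) | No | No |

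The plan gives no figure for this kind of bias, so there is none to reproduce. What follows is an illustration.

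**Inputs from the document**
- Planned size 300 per group and attrition 20% (2.11): 300 × 0.80 = 240 evaluable per group.
- Significance level 0.05 (2.12), taken as two-sided.

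**Assumed inputs**
- Between-group difference in the share of patients who start or change the drug: 5 or 10 percentage points.
- Drug effect on the outcome: 0.5, 1.0 or 1.33 SD. The last corresponds to a 40 mg/dl fall in LDL cholesterol with an SD of change of 30 mg/dl (40/30 = 1.33).
- No true moxibustion effect, normal approximation, no gain in precision from covariates.

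**Formulas**
- Bias in SD units = imbalance × drug effect.
- Standard error in SD units = √(2/240) = 0.0913. For LDL cholesterol, 30 × 0.0913 = 2.74 mg/dl.
- With k = bias / standard error, the chance of a significant result = P(Z > 1.96 − k) + P(Z < −1.96 − k).

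**Results**

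| Imbalance | Drug effect (SD) | Bias (SD) | k | False-positive rate |
|---|---|---|---|---|
| none | any | 0 | 0 | 5.0% |
| 5 points | 0.5 | 0.025 | 0.27 | 5.9% |
| 5 points | 1.0 | 0.050 | 0.55 | 8.5% |
| 5 points | 1.33 | 0.067 | 0.73 | 11% |
| 10 points | 0.5 | 0.050 | 0.55 | 8.5% |
| 10 points | 1.0 | 0.100 | 1.10 | 19.5% |
| 10 points | 1.33 | 0.133 | 1.46 | 31% |

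For the last row, the LDL shift is 0.10 × 40 = 4 mg/dl, and 4/2.74 = 1.46. Then P(Z > 0.50) + P(Z < −3.42) = 0.309 + 0.000, or 31%.

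Secondary outcomes are analysed per protocol, so fewer than 240 per group may contribute. That would lower k for the same bias and bring the rate closer to 5%, but would leave the bias itself unchanged.

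**The case against.** **The article is condensed.** The visit schedule figure and the case report forms are not shown, and a concomitant-drug page may exist. The month-0 list also omits the baseline laboratory values that the change outcomes need, which suggests that it is not exhaustive. This stands. A reader might infer that these drugs will go unrecorded and that no later adjustment is possible, but the text does not establish that. What remains is that every drug item listed is an antihypertensive, and that the covariate list is explicit and has no other drug term. Even if the data are collected, the stated model does not use them.

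**Comorbidity adjustment covers part of the problem.** This also stands, for treatment at entry. It does not reach changes during the year.

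**Drug changes during the study may belong to a pragmatic effect.** If being in one group leads to different prescribing, the difference is part of what the overall strategy does. That is fair, and it is a reason to report such changes by group rather than to adjust them away. It does not help where the difference comes from who chose which group, or where the result is read as moxibustion's own effect.

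**Tempting extensions without support**
- A reader might infer that the free consultations and examinations cause bias. Section 2.9 provides them equally: "Patients in both groups will receive free health consultations and physical examinations at each visit". Equal exposure does not by itself create a difference between groups.
- A reader might extend the point to herbal blood-pressure remedies and so to the primary outcomes. Nothing in the document says that their use differs between groups.
- A reader might extend it to the renal outcomes, "including urinary albumin (g/l) and serum creatinine (μmol/l) levels". Antihypertensive types are already recorded and adjusted for, and the document points to no other drug route.

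**Conclusion.** The point holds for the glucose and lipid secondary outcomes. As written, the stated model omits two known and measurable drug classes in groups formed by preference, and the comorbidity term closes the gap only in part. The bias could favour either group.

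Its size cannot be derived from the document. Under the assumptions shown, the false-positive rate would be about 6% to 31% instead of 5%. The upper end needs both a 10-point imbalance and a large drug effect of 1.33 SD; with a 5-point imbalance and an effect of 0.5 SD the inflation is slight. This is a risk that depends on drug use differing between groups, not a demonstrated error. It is a modest point, confined to secondary outcomes, in a study that already names its nonrandomized design as the main limitation.

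**What to change.** 1. **Section 2.8:** list glucose-lowering and lipid-lowering drugs (name, dose, start and stop) among the items recorded at months 0, 6 and 12 in both groups. If the case report form already has this page, say so.
2. **Section 2.12:** add baseline use of the relevant class to the ANCOVA for the matching outcome, that is, glucose-lowering drugs for glucose and HbA1c, and lipid-lowering drugs for the lipids.
3. **Reporting:** tabulate starts and changes of each class during the study by group, so that a reader can judge the laboratory differences against them.
4. **Any analysis restricted to patients without a drug change:** label it supportive. It conditions on an event after baseline that the outcome can itself trigger, for instance a high LDL value leading to a prescription, so it can introduce selection bias.

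The cost is slightly more data entry at three existing visits and a few extra covariates. The change concerns recording and analysis only and alters no patient's treatment.
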